
### Discontinuation Criteria

Participants will be discontinued from the study if they cannot safely continue the study based on any of the following criteria: (1) experience clinically significant worsening of depressive symptoms (50% increase in HRSD-24 scores from baseline on 2 consecutive ratings); (2) require in-patient hospitalization due to the presence of clinically significant suicidal ideation with imminent intent or attempted suicide; (3) develop clinically significant worsening of mood or physical symptoms (assessed by a study physician); (4) miss over 2 consecutive treatments during the study without the cause; (5) develop any medical illness that may be unstable; (6) experience a seizure; (7) become pregnant, or (8) withdraw consent.

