*Clinical assessments* will include (1) the MINI to clarify psychiatric inclusion and exclusion criteria; (2) the Antidepressant Treatment History Form (ATHF) to clarify on inclusion and exclusion criteria [26]; (3) the SSI will be administered at screening, baseline, weekly, and after treatment to confirm eligibility and to assess changes as a secondary outcome measure; (4) the HRSD-24, which will assess changes in depressive symptoms and will be administered at the baseline and after treatment; (5) the Young Mania Rating Scale (YMRS), which will be used to evaluate mania/hypomania symptoms at screening and throughout the study for eligibility and safety monitoring purposes [27]; and (6) World Health Organization Disability Assessment Schedule (WHODAS 2.0), which will be used as a standard measure of disability promoted and used at baseline and after treatment to assess changes in individual level of functioning [28].

*Neurophysiological assessments* will include (1) the Transcranial Magnetic Stimulation Adult Safety Screen to assess potential TMS risk factors; and (2) TMS-EMG/EEG. Our neurophysiological measures have been established and have a high test-retest reliability (ie, intraclass correlation >0.9) [18,19]. Data analysis will be performed using semiautomated methods developed and validated by our group [29]. TMS pulses will be administered to the left dorsolateral prefrontal cortex using a 7-cm figure-of-eight coil and 2 Magstim 200 stimulators (Magstim Company Ltd) connected via a BiStim module, and motor-evoked potential data will be collected using commercially available software (Signal; Cambridge Electronics). Each TMS session will include the establishment of the individual threshold for stimulation of motor cortex, and dorsolateral prefrontal cortex localization will be performed according to previously published methods [29,30]. The resting motor threshold will be determined by applying single pulses of TMS to the motor cortex while the coil is placed at the optimal position to elicit motor-evoked potentials from the right abductor pollicis brevis muscle. The resting motor threshold is defined as the minimum stimulus intensity that elicited a motor-evoked potential of >50 μV in more than 5 of the 10 trials [30].

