### Statistical Methods

Baseline participant characteristics will be reported and described using summary statistics—mean and SD for continuous data and number and proportion for categorical data. As the primary outcome is to assess feasibility, we will report on (1) recruitment numbers and attrition rates; (2) the number of individuals who experience side effects, and (3) the overall number and type of side effects. For neurophysiology, we will use an independent *t* test (paired 1-tailed) to compare components of TMS-evoked responses in the left dorsolateral prefrontal cortex in TMS-EEG data. In addition, we will apply a nonparametric cluster-based permutation test to investigate any significant changes in overall EEG channels. We will conduct a paired 1-tailed *t* test of the SSI and HRSD-24 scores from baseline to week 4 and monthly follow-up to assess preliminary clinical outcomes. We will also report the standardized mean difference as a measure of effect size (small: 0.2; medium: 0.5; large: 0.8).

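### Removing worsening participants from the study, combined with a two-point paired t test on SSI and HRSD-24, is liable to overstate improvement

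*Protocol article*

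**What the plan says.** Discontinuation Criteria (protocol article): "Participants will be discontinued from the study if they cannot safely continue the study based on any of the following criteria". Three of the eight criteria touch the outcomes that are later tested:

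- Criterion 1 is a worsening of depression, defined as "50% increase in HRSD-24 scores from baseline on 2 consecutive ratings".
- Criterion 2 applies to those who "require in-patient hospitalization due to the presence of clinically significant suicidal ideation with imminent intent or attempted suicide".
- Criterion 3 is clinically significant worsening of mood or of physical symptoms, as judged by a study physician.

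The other five (missed treatments, unstable medical illness, seizure, pregnancy, withdrawn consent) are largely unrelated to the scores. No sentence separates ending infusions from ending participation.

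Statistical Methods: "We will conduct a paired 1-tailed *t* test of the SSI and HRSD-24 scores from baseline to week 4 and monthly follow-up", and "We will also report the standardized mean difference as a measure of effect size". The section names no analysis set for this test and no rule for a missing later score.

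Data Collection Methods: "the SSI will be administered at screening, baseline, weekly, and after treatment". The same section places HRSD-24 only at baseline and after treatment, although its opening paragraph describes data collection as weekly during the infusions.

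Confidentiality: collection of new data ends when consent is withdrawn. Nothing comparable is said for participants discontinued on other grounds.

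**The concern.** A paired t test works on within-person differences. A participant with no week-4 score has no difference and drops out of that comparison, and likewise at follow-up. If the reason for the missing score is that the participant got worse, those left in the comparison did better on average than all who started. The mean change and the standardized mean difference then lean towards benefit. Weekly SSI scores from people who leave early would exist, but the stated test does not use them.

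The abstract says that the clinical outcomes are evaluated to inform a larger trial. An inflated effect size would make that trial too small to the extent that it is sized on this estimate. A later analysis plan can change the model, but it cannot recover ratings that were never taken, so continued rating has to be settled in the protocol.

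**Working it through.** **The plan's own figure.** The only computed number is the minimum sample size of 30. Sample Size gives no alpha, power, effect or SD, so it cannot be reproduced, and this point does not depend on it. A back-solve with d = (z_alpha + z_power)/√30, one-sided alpha 0.05 assumed, gives a detectable d of 0.45 at 80% power and 0.53 at 90%.

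**A hand illustration (assumed points).** Suppose the participants with both scores improve by 10 points and k of 30 are removed after worsening by 10. The paired test reports 10. The mean over all 30 is (10 × (30 − k) − 10 × k)/30:

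- k = 1: (290 − 10)/30 = 9.3
- k = 3: (270 − 30)/30 = 8.0
- k = 6: (240 − 60)/30 = 6.0

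**Simulation.** Inputs: n = 30 (Sample Size) and a paired one-tailed test (Statistical Methods). Assumed: alpha 0.05, normal improvement scores in units of the SD of change, the number removed k, and the correlation rho between the clinical course that triggers removal and the tested score. In each of 100,000 trials the k participants with the worst course are removed and the test is run on the rest. Rho = 1 is the extreme in which those removed are exactly those with the worst scores.

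True mean change 0:

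| Removed | Mean shift, rho 0.5 | Rejection | Mean shift, rho 1 | Rejection |
|---|---|---|---|---|
| 0 | 0.00 SD | 5.0% | 0.00 SD | 4.9% |
| 1 | 0.04 SD | 7.5% | 0.07 SD | 11.6% |
| 3 | 0.09 SD | 13.1% | 0.19 SD | 30.8% |
| 6 | 0.17 SD | 22.2% | 0.34 SD | 64.6% |

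The rho 0.5 shifts are half the rho 1 shifts (0.338/2 = 0.169; 0.186/2 = 0.093), as they should be in this model.

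True mean change 0.5 SD: the average reported standardized mean difference is 0.51 with none removed, 0.63 to 0.83 with 3 removed and 0.73 to 1.12 with 6 removed. Since sample size goes as 1/SMD², a trial sized on 0.63 instead of 0.51 would have (0.51/0.63)² = 66% of the participants needed. Sized on 0.83 it would have (0.51/0.83)² = 38%.

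**Chance that the problem arises at all.** P(at least one removal) = 1 − (1 − p)^30. For assumed individual risks p of 2%, 5% and 10% this is 46%, 79% and 96%.

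**Which criteria can act.** Criterion 1 needs two consecutive HRSD-24 ratings. On the baseline and after-treatment schedule it could not remove anyone before week 4, so outcome-related removal during treatment would come from criteria 2 and 3. If HRSD-24 is in fact rated weekly, criterion 1 can act as well.

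**The case against.** The best counter-case has five parts.

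- **The analysis set is not stated.** A reader might infer that the article commits to testing only completers. It does not: it names the test and is silent on missing scores, which a condensed article may leave to the full protocol or analysis plan. This stands, and the point is therefore conditional. What remains is that the stated test cannot use a person without a later score.
- **Contact does not end with dosing.** Harms has adverse events collected to 30 days after the last dose, and Confidentiality ends data collection only on withdrawn consent. This stands too: continued SSI and HRSD-24 rating is compatible with the text. It is also not provided for, and the wording used is discontinuation from the study.
- **The thresholds are high.** A reader might infer that everyone who worsens is removed. That goes too far: no SSI threshold exists, criterion 2 requires hospitalization for the stated reasons, and criterion 3 also covers physical symptoms. A separate simulation of criterion 1 alone, assuming weekly ratings, mean HRSD-24 of 20 to 30 and SD 5 to 7, with no true change, removed 0.2% to 3.9% and added 0.00 to 0.07 SD. Criteria 2 and 3 would add an amount that the documents do not let anyone calculate. The lower part of the range above may therefore be the more realistic one.
- **A mixed model is not a cure.** It is unbiased when removal depends on scores already observed. Removal by hospitalization or physician judgement between visits may depend on the unobserved score. This stands and shapes the fix.
- **The outcomes are tertiary and preliminary.** Limitations disclaims statistical significance as a goal, and attrition is reported. This lowers the weight of the rejection rates. It does not protect the effect estimate, and an attrition count does not correct it.

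**Conclusion.** The concern holds in conditional form. Removal from the study for reasons that overlap SSI and HRSD-24, followed by a test that needs both scores, is liable to overstate improvement if anyone is removed for worsening and not rated afterwards. The direction is towards benefit. The size rests on a removal rate and a correlation that the documents do not give: about 0.04 to 0.34 SD, with rejection under no change of about 7.5% to 65%, for 1 to 6 of 30 removed at rho 0.5 to 1 and one-tailed alpha 0.05. With none removed the bias is zero. A reader might go further and conclude that the trial will overstate its effect; without a removal rate the documents do not support that. The matter is worth correcting before analysis because the change is cheap and unrecorded ratings cannot be recovered. It does not affect the safety and feasibility counts that form the primary outcome.

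**What to change.** 1. In the protocol, separate stopping ketamine from leaving the study. Unless consent is withdrawn, keep the scheduled week-4 and follow-up SSI and HRSD-24 ratings for participants whose infusions have ended.
2. Analyse SSI with a repeated-measures mixed model (REML, visit as a factor, small-sample degrees of freedom) on all weekly and follow-up scores from everyone given at least one infusion. Report change at week 4 and at follow-up with 95% confidence intervals. Keep the paired t test as a sensitivity analysis.
3. Because removal under criteria 2 and 3 may not be missing at random, add a sensitivity analysis for both SSI and HRSD-24 that counts participants removed for worsening as not improved. Setting their change to zero is only the mildest version: with 3 removed and a spurious mean of 0.186 SD among the other 27, it gives 0.186 × 27/30 = 0.167 SD. Vary the assigned value from zero to a clear worsening.
4. Reconcile Discontinuation Criteria with Data Collection Methods on how often HRSD-24 is rated, since criterion 1 presupposes consecutive ratings. The criteria themselves are not questioned here.

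Cost: a few extra ratings, some protocol and analysis-plan wording, slightly more programming, and possibly a less favourable estimate.

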### Eligibility Criteria

*Inclusion criteria* are patients who (1) meet criteria for bipolar disorder according to DSM-V (Diagnostic and Statistical Manual of Mental Disorders, 5th edition) criteria as confirmed by the Mini-International Neuropsychiatric Interview (MINI) [22]; (2) meet criteria for a current depressive episode, confirmed with the 24-item Hamilton Rating Scale for Depression (HRSD-24) score of 14 and above [23]; (3) experiencing suicidal ideation as defined by a score of 9 or higher on the Scale for Suicide Ideation (SSI) [24,25]; (4) capable of providing consent; (5) outpatients; (6) able to speak and understand English; and (7) aged 24-65 years, inclusive.

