#### Dose Adjustment

If the first session is tolerated well and the patient has no side effects, the dose can be further increased up to (but not exceeding) 0.8 mg/kg. Participants will have a weekly follow-up with the study’s physician. The study physician will determine the exact doses on a case-by-case basis based on treatment tolerability, safety, and clinical response. From principal investigator’s (PI) previous clinical experience treating patients with ketamine, dose adjustment occurs within the first 1-3 sessions, and patients continue with stable doses following sessions 2 and 3. However, dose adjustment can also occur after session 3 if the participant experiences side effects with repeated infusions. The procedure around dose adjustment is a part of this trial’s feasibility; this information will be collected by the study physician during weekly follow-ups and incorporated into the research protocol for further studies in the future.

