#### Monitoring Schedule

All patients will stay on-site for the administration and monitoring period, calculated as 2 hours from the start of IV infusion per consensus guidelines in ketamine administration. Patients will stay in a separate private space and be provided with noise-cancellation headphones and an eye mask to minimize environmental disruptions. Patients will be closely monitored by available trained personnel, with a medical doctor present on-site for the entire supervision period. Specifically, IV induction will be performed under the direct supervision of an anesthesiologist or delegate and psychiatrist, who will remain present on-site for the entire duration of the 40-minute ketamine infusion. Trained personnel are available on-site to closely monitor the postinfusion period, where vital signs (ie, heart rate, blood pressure, oxygen saturation level) will be monitored every 30 minutes. Each patient will be closely monitored for the entire IV infusion duration and the postinfusion period for at least 2 hours. The overall time per treatment session is at least 2 hours starting from the time of infusion initiation. This includes the 40-minute infusion period and 80 minutes for postinfusion monitoring. Any adverse events will be managed by the medical team administering the treatment. If required, appropriate medications will be provided to manage treatment-related side effects and any adverse events as defined by clinical site policies and regulations. Clinical and neurophysiological assessments will be administered according to the trained research personnel’s schedule for study visits. There is a total of 16 study visits in this trial, which includes treatment sessions and follow-ups.

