### Data Collection Methods

Data will be collected on a baseline assessment, weekly during the course of IV ketamine, within a week after the completion of the intervention, and following 4 weeks for a final follow-up. Assessments will include psychiatric assessment, physical examination, and clinical assessments through manualized validated clinical scales (Multimedia Appendices 1 and 2).

*Psychiatric assessment* will include a consultation with a study physician to confirm a diagnosis. Demographic information, medical and psychiatric history, and concomitant medications will also be included.

A *physical examination* will include a physical exam performed by a study physician or a delegate, and blood work and electrocardiography for medical clearance according to standard clinical procedures also be reviewed by the study physician. Blood tests will include complete blood count with differential tests (white blood cells, red blood cells, hemoglobin, hematocrit, mean corpuscular volume, mean corpuscular hemoglobin, mean corpuscular hemoglobin concentration, red cell distribution width, mean platelet volume, platelet, nucleated red blood cell count, neutrophil count, lymphocyte count, monocyte count, eosinophil count, basophil count); blood chemistry test, including liver function (alanine transaminase and aspartate transaminase), kidney function (blood urea nitrogen and creatinine), and electrolytes (sodium, potassium, chloride, and phosphate); and thyroid function (thyroid-stimulating hormone). Study participants’ blood pressure will also be monitored before, during, and after treatment.

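### The HRSD-24 stopping rule needs two consecutive ratings, but the printed timing of the scale gives none during treatment, so as written the rule cannot avert any of the 8 infusions

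*Protocol article*

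**What the plan says.** Discontinuation Criteria, item 1, removes participants who "experience clinically significant worsening of depressive symptoms (50% increase in HRSD-24 scores from baseline on 2 consecutive ratings".

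The clinical assessments list under Data Collection Methods gives timings scale by scale:

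- Depression: "the HRSD-24, which will assess changes in depressive symptoms and will be administered at the baseline and after treatment".
- Suicidal ideation: "the SSI will be administered at screening, baseline, weekly, and after treatment to confirm eligibility".
- Mania (YMRS): "which will be used to evaluate mania/hypomania symptoms at screening and throughout the study for eligibility and safety monitoring purposes".

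Four other places bear on the timing:

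- The opening of Data Collection Methods says that, after baseline, data are collected "weekly during the course of IV ketamine, within a week after the completion of the intervention, and following 4 weeks for a final follow-up". It does not say which scales are used at which of these points.
- Statistical Methods plans paired tests of the SSI and HRSD-24 from baseline to week 4 and to a monthly follow-up.
- Eligibility Criteria requires a depressive episode "confirmed with the 24-item Hamilton Rating Scale for Depression (HRSD-24) score of 14 and above".
- Drug Administration and Scheduling sets two infusions a week for four weeks.

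**The concern.** The rule compares consecutive post-baseline HRSD-24 scores with baseline, so it needs at least two of them, and to protect a participant it needs them before the last infusion. The scale's own entry gives one post-baseline time point. That time point is after the whole course, not after each session: the SSI entry in the same list names weekly and post-treatment ratings as separate items. The list does assign different frequencies to different scales, and the HRSD-24 is not among those rated during the infusions.

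Item 1 is the only discontinuation criterion with a fixed depression-score threshold. Safety and attrition are both part of the primary outcome (Outcomes section), so it matters whether this rule can operate during treatment. There is a second mismatch: the HRSD-24 test at monthly follow-up has no corresponding rating in the list.

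**Working it through.** **Inputs**

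- Infusions: 2 per week × 4 weeks = 8, which agrees with the stated total (Drug Administration and Scheduling).
- Post-baseline ratings required by criterion 1: 2, consecutive.
- Printed HRSD-24 time points: baseline and after treatment (clinical assessments list), plus week 4 and monthly follow-up (Statistical Methods).
- Post-treatment visit: within 1 week of the end of the course. Final follow-up: at 4 weeks (Data Collection Methods).

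**Formula**

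Infusions that criterion 1 could avert = 8 − (infusions already given when the second consecutive post-baseline rating is made). If there is no second rating, the answer is 0.

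**Printed time points, read three ways**

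| Reading | Post-baseline ratings | Second rating falls | Infusions averted |
|---|---|---|---|
| (a) Assessments list alone | 1 | never | 0 |
| (b) Post-treatment + follow-up | 2 | 4 weeks after infusion 8, or up to 1 + 4 = 5 weeks if counted from the post-treatment visit | 8 − 8 = 0 |
| (c) Week 4 + post-treatment + follow-up, week 4 taken as a separate rating | 3 | post-treatment visit, 0 to 1 week after infusion 8 | 8 − 8 = 0 |

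Taking the week 4 rating before infusion 8 does not change the result, because the next rating still comes after infusion 8. All three readings share the premise that there is no weekly HRSD-24. They show that the result does not depend on how the end-of-treatment ratings are counted. They are not independent evidence that weekly ratings are absent.

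**Weekly ratings**

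The day of the weekly visit is not given, so two placements are shown.

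- Between the two sessions of each week: the first rating follows infusion 1 and the second follows infusion 3. Averted: 8 − 3 = 5.
- After the second session of each week, or before the first session from week 2 on: the second rating follows infusion 4. Averted: 8 − 4 = 4.

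**Would weekly ratings fit the visits?**

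Monitoring Schedule states: "There is a total of 16 study visits in this trial, which includes treatment sessions and follow-ups". Then 16 − 8 infusion visits = 8 others. One split that fits is screening (1) + baseline (1) + weekly (4) + post-treatment (1) + final follow-up (1) = 8. The article does not give this split; it is inferred. Dose Adjustment separately confirms weekly contact: "Participants will have a weekly follow-up with the" study physician.

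**The case against.** The strongest reply is that the assessments list is abbreviated and the real schedule is in the SPIRIT flowchart (Multimedia Appendix 1), which is not shown. The list does not say that the HRSD-24 is rated at no other time. It is demonstrably incomplete, since it also omits the eligibility HRSD-24 and the follow-up SSI that the article requires elsewhere. The HRSD-24 entry may give only outcome time points. General weekly data collection, weekly physician follow-up and the stopping rule itself all make a weekly HRSD-24 plausible. All of this stands, and it makes a reporting slip a real possibility. It does not remove the conflict: the article prints both the rule and the scale's timing, the two do not fit, and the same list does say weekly for the SSI.

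The second reply is that participants are protected in other ways. Criterion 3 allows a physician to stop treatment for clinically significant worsening of mood, with no score threshold and no second rating. Criterion 2 covers hospitalization for suicidal ideation with imminent intent or an attempt. The SSI is weekly, and the YMRS is rated throughout for safety. This also stands. No infusion is shown to be given that would otherwise have been stopped, so the counts describe when criterion 1 can act and do not estimate harm. Criterion 3 is a judgement, however, and does not make criterion 1 workable.

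**Conclusion.** The concern holds as an inconsistency within the article. On the printed HRSD-24 time points, criterion 1 can avert 0 of 8 infusions; with weekly ratings it could avert up to 4 or 5, depending on the visit day. The zero is conditional on the assessments list reflecting what is done. If the unshown flowchart has weekly HRSD-24 ratings, only the sentence in the list is wrong.

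The weight is minor to moderate. What is lost is the one numeric depression threshold among the stopping rules, not safety monitoring as a whole. It is worth fixing because the rule concerns safety in acutely suicidal participants and the correction is cheap. Confidence is medium, because the full schedule cannot be seen.

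**What to change.** In the clinical assessments list, state that the HRSD-24 is rated at eligibility, at baseline, at each weekly visit during the infusions, after treatment and at final follow-up. Criterion 1 can then act from about week 2, and the follow-up test has its rating.

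**Cost if the full schedule already contains these ratings:** one wording correction.

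**Cost if it does not:** an amendment and 3 extra ratings per participant (weeks 1 to 3), or 4 if the week 4 rating is not the post-treatment one. That is at most 3 × 30 = 90 to 4 × 30 = 120 ratings. They can be done at the weekly physician follow-ups that already take place, so no visit is added. The eligibility and follow-up ratings are not counted as extra, because Eligibility Criteria and Statistical Methods already require them.
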